### Blinding

Additionally, there was no possibility of blinding the researcher due to the organization of the training sessions and the conduct of the interventions. However, medical center staff will be blinded. Blinding is also done when dividing the participants into two control and intervention groups and during the statistical analysis of the data. Training sessions for the intervention group will take place on days when people in the control group are not present at the clinic so that information is not randomly delivered to them and they do not communicate with each other. This issue will be the reason for the long process (about 2 years) of this research.

### Statistical analysis

The analytical method used in this study will be quantitative. The information recorded in the questionnaire will be entered into the SPSS program at each stage and data analysis will be conducted after the research process is completed. Categorical variables will be reported based on frequency, and quantitative variables will be reported as mean (SD). The ANOVA test will be used for quantitative variables that have a normal distribution, and the Friedman test will be used for quantitative variables that do not have a normal distribution. The effectiveness of the intervention will be determined using an ANOVA test and the impact of demographic variables on factors measured using a logistic regression model. Statistical analyses will be performed using IBM-SPSS 22. For all analyses, P values  < 0.05 are considered statistically significant.

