3	Addressing the role of perceived behavioral control in childbearing	PowerPoint Pamphlet of the third session Video	1) Review of previous session (5 min) 2) Giving information on requirements and cares for becoming pregnant, prenatal cares, and care of newborn (30 min) 3) Presenting a short video which shows how a baby develops (5 min) Showing how to provide care during pregnancy and for newborn (10 min) 4) Showing videos of care of newborn (10 min) 5) Question and answer (10 min)
4	Addressing the behavioral intention and explaining how childbearing will change couple’s life	PowerPoint Pamphlet of the fourth session Video	1) Reviewing previous session (5 min) 2) Giving information on advantages of having a child from cultural, religious and social perspectives (10 min) 3) Showing videos of successful childbearing expression (10 min) 4) Question and answer (10 min)

Participants who meet the inclusion criteria will first complete a childbearing intentions questionnaire, which will be designed based on the stages of the change model and the samples who are in the pre-contemplation and contemplation stage will be included in the study. After this step, by accessing the Sib system “a national system that records health information of individuals”, couples who have been married for 2 years without children and meet the inclusion criteria will be selected. Then, 60 samples (30 pairs) will be selected through a random number table and will be randomly divided into 2 groups: control and intervention.

Teaching methods will include conferences, discussions, Q&A, and document distribution. During the classes, the researcher does not impose personal views and attitudes on the couple. It is explained to them that all decisions about having children are based entirely on their opinions and considerations and there is no coercion. They must also fill in the questionnaires without concern and honesty because their answers do not affect the quantity and quality of the treatment, and whenever they do not want to participate in the study, they can refuse to continue.

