### Sample size

To provide a power of 95% with a 99% confidence interval using the following formula and considering the mean and standard deviation of intention to have based on the findings of a similar study by Moghaddam et al. [36]. The sample size was estimated at 12, and then considering 20% attrition, we plan to recruit 15 couples per group and a total of 30 couples study participants.$$n=\frac{{( {z}_{1-\frac{\alpha }{2}}+ {z}_{1-\beta } )}^{2} ({s}_{1}^{2}+ {s}_{2}^{2})}{{({\mu }_{1}- {\mu }_{2})}^{2}}=\frac{2.1664 \times 14.82}{2.6896}=\frac{32.106048}{2.6896}=11.93 \cong 12$$

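### Each score's normality decides between ANOVA and Friedman, which conflicts with the unconditional ANOVA sentence and can send attitude to a test that does not compare the arms

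*Protocol article*

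**What the plan says.** The Statistical analysis section of the protocol article gives two rules for quantitative outcomes.

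- A conditional rule: "The ANOVA test will be used for quantitative variables that have a normal distribution". Variables judged non-normal go to Friedman instead.
- An unconditional rule, in the next sentence: "The effectiveness of the intervention will be determined using an ANOVA test".

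On timing, it says that "data analysis will be conducted after the research process is completed". On the threshold, it says: "For all analyses, P values < 0.05 are considered statistically significant".

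The scores concerned are knowledge, attitude, subjective norms and perceived behavioural control (The study instruments), plus an intention score if one is formed (Secondary aims lists behavioural intention). Attitude is a 15-question score and the second part of the primary outcome. The first part is movement through the stages of change, which is an ordered category.

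**The concern.** The conditional rule lets the observed distribution of each score pick its test. For a score judged non-normal, one sentence points to Friedman and the next to ANOVA, and nothing says which result counts. Attitude falls under both rules.

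The two tests do not answer the same question. Friedman ranks each participant's repeated assessments against one another and has no term for arm. If a score goes down that branch, the P value concerns change over time, not the effect of the education programme. In a trial where both arms might improve simply from repeated questioning, that difference could reverse the conclusion.

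The criterion is also slightly misdirected: ANOVA needs roughly normal residuals, not a normal variable.

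**Working it through.** **Plan figures used.** No figure in the article bears directly on this point; the sample size only supplies n. The printed calculation is 2.1664 × 14.82 / 2.6896 = 11.94 (printed as 11.93), so 12 per group, and 12 / (1 − 0.20) = 15. The article states: "The sample size was estimated at 12, and then considering 20% attrition, we plan to recruit 15 couples per group". The Interventions section adds that "60 samples (30 pairs) will be selected through a random number table". A normality check could therefore see 24 couples (2 × 12, after attrition), 30 couples, 48 people (2 × 24) or 60 people.

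**Assumption.** No normality test is named. Shapiro-Wilk at 5% is assumed below, with all values in a check treated as independent, although spouses are not.

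**Step 1: truly normal scores.** Each check wrongly rejects with probability 0.05. With k independent checks, one per score, the chance of at least one diversion is 1 − 0.95^k.
- k = 4 named scores: 1 − 0.95^4 = 0.185, about 19%.
- k = 5 (with an intention score): 1 − 0.95^5 = 0.226, about 23%.

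Independence hardly drives this. Simulating four variables correlated at 0.6 gave 16% to 20% for n = 12 to 60 (1,500 runs per case).

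**Step 2: a skewed score.** For a gamma variable with shape 4 (skewness 2/√4 = 1), Shapiro-Wilk at 5% rejected in these proportions of 3,000 simulations:

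| Values checked | Diverted to Friedman |
|---|---|
| 24 | 36% |
| 30 | 46% |
| 48 | 67% |
| 60 | 78% |

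The same underlying score could go either way, depending on the sample and on whether couples or individuals are checked.

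**Step 3: what diversion does.** Inputs: 15 per arm, four assessments (as in Data collection), within-person correlation 0.6 (assumed), 2,000 runs per case. Each arm shifts by the stated amount from baseline to all later assessments. Friedman is run on both arms pooled; the comparator is a between-arm t-test of change from baseline to the last assessment. The table gives rejection rates at 0.05.

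| Shift, arm 1 / arm 2 (SD) | Friedman | Between-arm test |
|---|---|---|
| 0 / 0 | 4.9% | 4.5% |
| +0.8 / +0.8 (no arm effect) | 99% | 5% |
| +0.8 / −0.8 (large arm effect) | 2% | 99.8% |

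**Step 4: is the switch itself the harm?** Replace Friedman with Mann-Whitney, which does compare arms, and use a t-test otherwise. Under the null, type I error after the switch stayed between 3.8% and 5.7% across the simulations run. In a set with 12 or 15 per arm, covering normal, skewness-1 and exponential scores, the two tests gave the same significance verdict in 97% to 98% of runs. The damage therefore comes from the fallback this plan names, not from pre-testing as such.

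**Step 5: variable versus residual.** With normal arms 3 SD apart, pooled scores failed Shapiro-Wilk in about 18% of runs at 15 per arm and 45% at 30 per arm, although the ANOVA assumption held exactly. At gaps of 1 to 2 SD the rate was no more than about 5%, so this matters only in extreme cases.

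**The case against.** The strongest reply is that ANOVA is named for effectiveness without condition, so the efficacy test is settled. On that view the ANOVA/Friedman pair merely describes within-arm change over time. This is a possible intention, but the text does not limit the first rule to within-arm comparisons, and attitude is a quantitative variable under either sentence. The reply does defeat a stronger reading: a reader might infer that the primary analysis is left open until the data are seen. The documents do not support that. A test is named; the defect is that another sentence contradicts it for non-normal scores. Nor does the rule clearly govern stage of change, which is an ordered category.

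A reader might also infer that different time points of one score would be split between tests, and multiply the checks: 1 − 0.95^15 = 54% for five scores at three assessments, or 1 − 0.95^20 = 64% at four. The documents do not support this either. The rule is written per variable, Friedman takes all assessments of a variable together, and repeated checks on the same people are not independent.

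Two further objections stand. Choosing between a parametric and a rank test by normality is common in small questionnaire trials and, with a between-arm fallback, costs almost nothing in type I error (step 4). And the normality test, its threshold and whether raw scores or residuals are checked are details that an article may leave to a fuller document; their absence is not the complaint. The complaint is the rule that is stated.

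**Conclusion.** The point holds, with limited scope. The Statistical analysis section contains a data-driven rule and an unconditional rule that conflict for any non-normal quantitative score, including attitude. The chance of the conflict arising is about 19% to 23% even if all 4 to 5 scores are truly normal, and about 36% to 78% for a single score with skewness 1. These figures assume Shapiro-Wilk at 5%; the first range also treats scores as independent, and the second depends on whether 24 or up to 60 values are checked. They are probabilities, not a forecast that scores will be split.

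The consequence is serious only because the fallback is Friedman, which can reject almost always when the arms do not differ and almost never when they differ greatly. It is a small drafting defect that is cheap to remove and worth removing before analysis.

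**What to change.** Delete the normality-based choice and merge the two sentences into one rule for all quantitative scores. For example:

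> Knowledge, attitude, subjective norms, perceived behavioural control and any intention score will be compared between arms by the same pre-specified analysis whatever their observed distribution: either ANOVA on couple-level means, or a mixed model with couple as a random effect. Residuals will be inspected but will not change the analysis. A permutation P value that re-randomises whole couples will be reported as a sensitivity analysis for every score.

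The authors should choose one of the two options before the data are seen. If a single mixed model covers several assessments, it also needs a person-level term within couple. If Friedman is kept, it should be labelled as a within-arm description of change over time, with no role in judging effectiveness. The ordered stage-of-change outcome should be kept outside this sentence.

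The cost is one or two sentences and a short permutation script. Data collection, sample size and significance level are unaffected.

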### Trial design

This study is a parallel group clinical trial. The TTM and TPB are used for training and measuring outcomes. The participants are childless couples who have been married for at least 2 years and are in the pre-contemplation and contemplation stages of having children. A diagram of the research process is shown in Fig. 1. After the intervention, their attitudes, subjective norms, and perceived level of control over childbearing behavior will be compared with before the intervention, to determine whether the interventions lead couples out of the pre-contemplation stage to later stages or not. The duration of this study is approximately 2 years from the beginning of the training to the end of the follow-up (6 months after the intervention). This study was approved by the Ethics Committee (Ethics Code: IR.TUMS.FNM.REC.1402.013) of Tehran Medical University. Informed consent is completed by all participants after an explanation of the objectives of the study, the research process, and the follow-up period.

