### Data collection

A questionnaire designed by researchers will be used to assess the impact of this intervention on people's attitudes and subjective norms. This questionnaire is administered to assess the three components of attitude, subjective norms, and perceived behavioral control and to determine how the change process is carried out in four stages: before the intervention (S0), immediately after the intervention (S1), 1 month after the intervention (S2) and 6 months after the procedure (S3).

The questions prepared for this study will be designed based on: Research objectives, two mentioned models, and teaching content. Once designed by the researcher, it will be sent to specialist teachers and their validity and reliability will be assessed. Questions in the S0 phase are filled in person at the clinic, but to allow people to better receive questions and answers without the need to visit the clinic, the questions asked in the questionnaire will be sent online in the later stages. This Iranian online system is called Porsline, and at an agreed time, a link to the survey is sent to participants, and the researcher monitors their responses by phone.

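### For non-normal scores the plan names only the Friedman test, which has no group term and so cannot compare intervention with control

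*Protocol article*

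**What the plan says.** The design is comparative: "This study is a parallel group clinical trial" (Trial design), with couples randomised to intervention or control. The same section then describes the assessment of the outcomes as a contrast over time: "After the intervention, their attitudes, subjective norms, and perceived level of control over childbearing behavior will be compared with before the intervention". It does not mention the control group in that sentence.

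The Statistical analysis section chooses the test by distribution. For normal scores: "The ANOVA test will be used for quantitative variables that have a normal distribution". For the rest: "the Friedman test will be used for quantitative variables that do not have a normal distribution". It adds that "The effectiveness of the intervention will be determined using an ANOVA test", without saying whether the factor is group, time or their interaction. No non-parametric test that compares the two arms is named.

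Data collection lists four time points: before, immediately after, one month after and six months after the intervention. The first is completed in person. After that, "the questions asked in the questionnaire will be sent online in the later stages".

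**The concern.** In a randomised trial, evidence of effect comes from the contrast between arms. The Friedman test asks a different question: do the values of the same people differ between visits? If attitude, a subjective norms score, perceived control or knowledge is not normally distributed, the distribution rule takes it out of ANOVA and into Friedman. No stated test then involves the control arm.

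A change in both arms is plausible here without any effect of the sessions. The mode of completion changes after baseline, for both arms as far as the text says, and the same questionnaires are answered repeatedly. Comparison with the control arm removes such shared changes, and a within-arm test cannot. A significant Friedman result in the intervention arm could then be reported as an effect of the education when it reflects the passage of time or the change to online completion.

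**Working it through.** The plan gives no figure to reproduce on this point. The check is first structural and then illustrative.

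**Structure of the test.** With n participants, k visits and R_j the sum over participants of the within-person ranks at visit j:

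Q = 12 / (n k (k+1)) × Σ R_j² − 3 n (k+1), referred to chi-square with k − 1 degrees of freedom.

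The terms are n, k and the rank sums by visit. Arm does not appear. Run within one arm, Q uses nothing from the other. Run on both arms pooled, Q is unchanged if the arm labels are exchanged.

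*Constructed example.* Take n = 15 in each arm and k = 4, and let both arms have the same rank sums: 24 at baseline and 42 at each later visit (24 + 3 × 42 = 150 = 15 × 10, as required). Then Q = 12/(15 × 4 × 5) × (576 + 3 × 1764) − 3 × 15 × 5 = 0.04 × 5868 − 225 = 9.72 on 3 degrees of freedom, p about 0.02. Each arm is significant although their rank sums are identical.

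**Illustration by simulation.**

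Inputs from the protocol article:
- two parallel arms (Trial design);
- four visits (Data collection; the abstract counts three);
- 12 units per arm as calculated and 15 after the attrition allowance (Sample size);
- significance level 0.05 (Statistical analysis).

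Assumptions not in the documents:
- the same shift from baseline to all later visits in both arms, of 0, 0.5, 0.8 or 1.0 SD;
- within-person correlation 0.5;
- normal scores;
- one independent score per unit;
- no intervention effect.

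There were 2,000 runs per setting. The Monte Carlo standard error at 5% is √(0.05 × 0.95 / 2000) = 0.5 percentage points. Percentage of runs with p < 0.05:

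| Units per arm | Common shift (SD) | Friedman, intervention arm | Friedman, arms pooled | Before-after Wilcoxon, intervention arm | Mann-Whitney on change, between arms | Group-by-time F test |
|---|---|---|---|---|---|---|
| 12 | 0 | 5.0 | 6.2 | 4.8 | 4.5 | 5.8 |
| 12 | 0.5 | 25.0 | 55.2 | 31.8 | 4.2 | 4.4 |
| 12 | 0.8 | 63.2 | 94.4 | 67.8 | 5.2 | 6.1 |
| 12 | 1.0 | 82.7 | 99.3 | 84.4 | 3.5 | 4.6 |
| 15 | 0 | 4.8 | 4.9 | 5.0 | 3.8 | 4.5 |
| 15 | 0.5 | 35.6 | 66.6 | 40.8 | 4.2 | 5.8 |
| 15 | 0.8 | 75.5 | 97.6 | 79.2 | 4.5 | 4.1 |
| 15 | 1.0 | 91.0 | 100.0 | 94.0 | 4.6 | 5.0 |

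A separate simulation on the same pattern (3,000 runs, 12 units) gave 26.8% for Friedman at a shift of 0.5 SD and 11.7% at 0.3 SD.

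Comparing the two within-arm results does not repair this. With 15 per arm, significance in the intervention arm but not in control occurred in 23.6%, 19.4% and 7.2% of runs at shifts of 0.5, 0.8 and 1.0 SD, again with no true effect.

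**The case against.** The strongest reply is that Friedman is never called the effectiveness test. The sentence that designates that test names ANOVA, and its factors may include group or group-by-time. The sample size formula has the form for two independent means, with two variances over a squared difference of means, and the size is given per group. Trial design opens by calling the trial parallel-group, and comparing with baseline is compatible with then comparing those changes between arms. A condensed article may also leave model terms to a fuller document.

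Much of this stands. A reader might infer that no between-group analysis is planned, that the control group goes unused, or that before-versus-after is the trial's main comparison. The documents support none of these: the ANOVA is unspecified rather than shown to be within-group, and the sample size formula points to a contrast between two means.

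It does not rescue the non-normal scores. The rule that sends them to Friedman is stated, and it takes them out of ANOVA. A fuller plan would have to replace that choice, not merely add detail to it.

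The illustration also has fair limits. The shift and the correlation are assumed. The rates count as errors only if a within-arm p-value is read as the effect. The simulated scores were normal, whereas the plan would use Friedman for non-normal ones, so the rates are indicative only. Nor is it shown that the scores will be non-normal: the attitude, norms and control scales have 15, 10 and 25 items, and their totals may be close to normal.

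A reader might also suspect that the logistic regression in the same section is misapplied. The wording is ambiguous, stage of change is categorical, and one secondary aim relates demographics to intention, so the text does not show an error there.

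**Conclusion.** The point holds for quantitative scores that are not normally distributed. For these the stated method cannot test the randomised contrast. That follows from the form of the Friedman statistic and depends on no assumption. The before-versus-after sentence under Trial design adds to the risk that a within-arm change is reported as an effect.

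The point does not extend to normally distributed scores, where the plan is unclear about the ANOVA's factors but not shown to be wrong.

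How often a shared change would mislead depends on figures that the documents do not give. At an assumed common shift of 0.5 SD and correlation 0.5, Friedman in the intervention arm rejects in about 25% to 36% of trials with 12 to 15 units and no intervention effect. At 0.3 SD it is about 12% with 12 units. In the settings tabulated, the between-arm tests stay between 3.5% and 6.1%.

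**What to change.** Four changes of wording:

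1. In Statistical analysis, keep the Friedman test for within-arm description only and say that it is not evidence of an intervention effect.
2. For non-normal scores, name a between-arm test of change from baseline at a stated time point that treats the couple as the unit. For example, average the two spouses' changes, then apply a Mann-Whitney test or a permutation of arm labels across couples.
3. State that the effectiveness ANOVA tests group or group-by-time.
4. In Trial design, replace the before-versus-after sentence with one saying that changes from baseline are compared between intervention and control.

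The cost is analysis wording only. No visit, questionnaire or additional couple is needed, and the change should be made before the data are analysed. The between-arm test will reject less often than the within-arm one. In one simulated setting (15 per arm, common shift 0.5 SD, added intervention effect 1 SD, correlation 0.5) Mann-Whitney on change rejected in 71% of runs and group-by-time in 79%, against 99.8% for Friedman in the intervention arm. That last figure credits the common change to the intervention, so it is not a power advantage for the trial's question.

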**Methods:**

Thirty couples (intervention, n = 15; control, n = 15) will be enrolled in this cluster randomized controlled trial. After collecting baseline data and separating participants in the pre-contemplation and contemplation stages based on the TTM, the samples were randomly assigned to the intervention and control groups. The intervention group will receive 60-min training based on TPB components for 4 weeks. The first follow-up assessment was performed immediately after the intervention and the final assessment 6 months later. For all 3 time assessments, three questionnaires will be used: The knowledge questionnaire, the TTM, and the TPB questionnaire. The most important consequences are changes in knowledge, attitudes, subjective norms, perceived behavioral control, and stages of intentions to have children.

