#### Trans-theoretical model questionnaire (TTM)

At the beginning of the study, to find out whether the person meets the criteria to enter the study or not, the participant must fill out a questionnaire about the stages of change, and whether they are in the pre-contemplation or contemplation stage, it is included in the study. This questionnaire is designed based on the stages of the change model and includes 7 questions to determine which stage the person is in. After the intervention, each participant's level of change toward the next steps in behavioral intentions will be measured using this questionnaire according to specific steps.

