### Randomization

After checking the participants' basic information regarding the inclusion criteria, a list will be prepared, and then, to randomly divide them into two intervention and control groups, samples will be allocated into two groups based on the Random Number Table. Because interventions aim to educate people, participants cannot be blinded. The people targeted by the intervention are therefore aware of the group to which they belong.

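### A trial labelled cluster randomised, with two spouses measured per couple, names only an ANOVA for effectiveness, with no couple term, couple-level score or stated unit of analysis

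*Protocol article*

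**What the plan says.** All references are to the protocol article.

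- **Design label.** According to the abstract, thirty couples, 15 per arm, "will be enrolled in this cluster randomized controlled trial". The title uses the same label. Under Trial design the text reads "This study is a parallel group clinical trial" and clusters are not mentioned. No section defines the cluster.
- **Recruitment unit.** Sample size: "we plan to recruit 15 couples per group and a total of 30 couples study participants".
- **Allocation.** Interventions: "Then, 60 samples (30 pairs) will be selected through a random number table and will be randomly divided into 2 groups". Randomization: "samples will be allocated into two groups based on the Random Number Table".
- **Measurement.** The stage questionnaire classifies the person, and afterwards each participant's "level of change toward the next steps in behavioral intentions will be measured using this questionnaire". The planned-behaviour questionnaire has a part on individual attitudes. No section describes a score for the couple, or how two spouses at different stages would be combined.
- **Analysis.** Statistical analysis: "The effectiveness of the intervention will be determined using an ANOVA test". Friedman's test is named for non-normal quantitative variables and logistic regression for demographic influences, with significance at P < 0.05. No couple effect, couple summary or ICC is mentioned, and the unit of analysis is not given.

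**The concern.** Two spouses answering questions about having a child together, who attend the same sessions together, can hardly be expected to give unrelated answers. An ordinary ANOVA assumes independent observations. A design declared as clustered produces two records per cluster, and the only effectiveness test named has no place for the cluster.

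If that test is run on person-level records from intact couples, the standard error of the treatment difference is too small. Intervals are then too narrow and false-positive findings too frequent. This bears on the analysis that decides whether the programme works, in a trial whose Discussion hopes to inform national policy. The article does not merely leave detail to a later document: it names the test, and the test as named does not match the declared design.

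**Working it through.** **1. The plan's own figure.** From Sample size: 2.1664 × 14.82 / 2.6896 = 32.106 / 2.6896 = 11.94, rounded up to 12; 12 / (1 − 0.20) = 15 per group, counted in couples. The formula has no ICC or design effect. It therefore supplies the unit (couples) but no correlation. Whether 12 follows from the stated power and confidence is a separate matter that is not used here.

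**2. Inputs.** 15 couples per arm and 60 people (Sample size, Interventions), so cluster size m = 2. Alpha is 0.05 (Statistical analysis); two-sided is assumed, because the section does not say. The within-couple ICC is not given and is varied from 0.1 to 1.0.

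**3. Formulas**, for couples allocated intact and analysed as 60 independent people at one time point:

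- Design effect = 1 + (m − 1) × ICC = 1 + ICC.
- Effective number of people = 60 / (1 + ICC).
- Correct interval width relative to the naive one = √(1 + ICC).
- Actual type I error = 2 × [1 − Φ(1.96 / √(1 + ICC))].

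At ICC 0.2: 1.96 / √1.2 = 1.789, giving 0.0736. At ICC 0.5: 1.96 / √1.5 = 1.600, giving 0.1095.

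**4. Results.** The simulations used 15 couples per arm and 60,000 replicates per row.

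| Assumed ICC | Effective n | Width factor | Type I error, formula | Simulated, 60 individuals | Simulated, couple means |
|---|---|---|---|---|---|
| 0.1 | 54.5 | 1.05 | 0.0617 | 0.0606 | 0.0485 |
| 0.2 | 50.0 | 1.10 | 0.0736 | 0.0730 | 0.0498 |
| 0.3 | 46.2 | 1.14 | 0.0856 | 0.0852 | 0.0499 |
| 0.5 | 40.0 | 1.22 | 0.1095 | 0.1150 | 0.0512 |
| 0.7 | 35.3 | 1.30 | 0.1328 | 0.1361 | 0.0484 |
| 1.0 | 30.0 | 1.41 | 0.1658 | 0.1753 | 0.0500 |

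With 12 couples per arm, the number left after the planned 20% attrition, the simulated individual-level figures are similar: 0.072 at ICC 0.2 and 0.112 at ICC 0.5.

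**5. Which ICC.** The table treats one comparison at one time. The protocol has repeated assessments and words its outcomes as change. For a change-score or group-by-time analysis the same formula applies, but with the within-couple correlation of change, which may differ from that of the scores themselves.

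**6. The other reading of the allocation.** If the 60 people were randomised one by one, with spouses free to fall in different arms, the simulated type I error of the individual-level test is 0.049 to 0.051 at ICC 0.3, 0.5 and 0.8 (40,000 replicates each). The inflation arises only when couples are kept together.

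**The case against.** **The unit of analysis is not stated.** A reader might infer that the plan treats spouses as independent. The Statistical analysis section does not say so. The abstract and Sample size count couples, and the primary outcomes are worded in terms of couples. An ANOVA on one score per couple would hold 5%, as the last column of the table shows. This stands, and it is why the figures above are conditional. It does not dispose of the point: stage and attitude are measured on the person and no couple score is described anywhere, so the person-level analysis is the easiest one to run under the present wording.

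**Model terms belong in an analysis plan that is not shown.** This is fair for fine detail, such as the exact model for stage. It is weaker for the unit of analysis in a trial that declares itself cluster randomised and then names its effectiveness test.

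**The false-positive rate doubles.** A reader might infer this as a fixed result. Doubling (0.098 to 0.121) needs an ICC of about 0.4 to 0.6, which the documents do not give.

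**Individuals are randomised and spouses may be split.** A reader might infer this from the word samples, used alone under Randomization and for 60 people under Interventions. But the 60 are described there as 30 pairs, each group is 15 couples, and the sessions are held with couples present. Splitting is an unlikely reading that needs one clarifying sentence. Nor does the allocation wording cause the inflation; step 6 shows that the two problems are alternatives.

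**Conclusion.** The point holds as a conditional one. The declared design is clustered, the couple is the only cluster the text supports, each spouse is measured, and the named effectiveness test makes no provision for the couple. If couples are allocated intact and all 60 person-level scores enter the ANOVA, the actual type I error of a nominal two-sided 5% test is about 6% to 17% for an ICC between 0.1 and 1.0, and intervals should be about 5% to 41% wider than the naive ones. The range rests on an assumed ICC and on a single two-group comparison; for change or group-by-time analyses the ICC of change must be substituted. An analysis at couple level removes the problem.

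**What to change.** **Statistical analysis.** State the unit of analysis and how the two records per couple are handled, in one of two ways:

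- a linear mixed model with a couple random effect, with repeated visits nested in person, and small-sample degrees of freedom. If the treatment effect is a group-by-time contrast, the couple effect should be allowed to vary by visit, or follow-up scores should be modelled with baseline as a covariate, because a constant couple intercept cancels out of change;
- an analysis of couple means, or couple mean changes, 15 v 15, with a rule for couples in which only one spouse responds.

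Account for couple clustering in the stage and logistic analyses as well.

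**Interventions and Randomization.** As a clarification, state that the couple is the unit of randomisation and that both spouses go to the same arm. Align Trial design with the title.

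**Cost.** Wording only; recruitment and procedures are unchanged, and mixed models are available in the planned SPSS package. The downside is that p-values and intervals become somewhat less favourable.
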